## Abstract

**Introduction:**

Therapeutic education is expanding in the management of Alzheimer’s disease (AD) patients. Several studies have revealed a positive impact of therapeutic educational programmes on the caregiver’s burden and/or quality of life. However, to date, no study has evaluated its impact on the quality of life of the AD patient.

**Methods:**

The THERAD study (THerapeutic Education in Alzheimer’s Disease) is a 12-month randomised controlled trial that started in January 2013. This paper describes the study protocol. THERAD plans to enroll 170 dyads (AD patient and caregiver) on the basis of the following criteria: patient at a mild to moderately severe stage of AD, living at home, receiving support from a family caregiver. The main outcome is the patient’s quality of life assessed by the Logsdon QoL-AD scale at 2 months, reported by the caregiver. The study is being led by geriatricians trained in therapeutic education at Toulouse University Hospital in France. To date, 107 caregiver/patient dyads have been recruited.

**Conclusion:**

This is the first trial designed to assess the specific impact of a therapeutic educational programme on the AD patient’s quality of life. The final results will be available in 2015.

**Trial registration:**

[ClinicalTrials.gov: NCT01796314] Registered 19 February 2013

## Introduction

Therapeutic education in the care of Alzheimer’s disease (AD)-affected patients has only recently been instigated [1]-[8]. Indeed, it seems difficult to implement such programmes because of the following two characteristics of the disease: memory loss and anosognosia. The patient’s abilities to acquire skills and modify his/her behaviour are often deeply affected by the disease. The caregiver, who bears a substantial burden that can have adverse effects on his/her physical and mental health, consequently appears to be the real beneficiary of those approaches [5],[6]. For this reason, most of the studies in the field of therapeutic education in AD have focused on the impact of therapeutic educational programmes on the caregiver’s outcomes [2],[4]-[8]. Several works have demonstrated positive results, such as an improvement in the caregiver’s quality of life (QoL) [7] and a decrease in their depression [5],[6] and burden [2]. As regards the AD patient, a few studies have evaluated the effectiveness of psychoeducational interventions on his/her behaviour [9], functional autonomy [3] or cognitive status [1]. The large majority of studies have evaluated multidimensional interventions including educational activities (associated, as appropriate, with respite, psychological support and/or pharmacological treatment). Two trials showed that this type of multidimensional intervention decreases the behavioural and psychological symptoms of dementia [9],[10].

A meta-analysis suggests that the most effective interventions for both patient (behavioural and psychological symptoms of dementia) and caregiver (burden) are those with an intensive psychoeducational programme for caregivers accompanied by a follow-up [11]. In a literature review [12], four studies demonstrated positive results of combined intervention programmes including psychoeducational components on both patients and caregivers [13]-[16]. In these programmes, the mental health of the AD patient was improved [13],[14] and admission to long-stay care was delayed [15],[16]. Lastly, among more recent studies, the Danish Alzheimer Intervention Study randomised controlled trial conducted in Denmark has demonstrated that a psychosocial counselling and support programme for outpatients with mild AD and their primary caregivers leads to a small, although nonsignificant, difference in the patient’s depression (assessed by the Cornell depression scale score [17]) in the intervention group [1].

These studies have not specifically studied the patients’ QoL as an outcome – except for the Danish Alzheimer Intervention Study, but its intervention was not exclusively educative – and were not methodologically designed for this purpose. In the Therapeutic Education in Alzheimer’s Disease (THERAD) study we chose to evaluate the impact of an educational programme on the AD patients’ QoL, given the results in the literature and those of a feasibility study we have conducted. QoL seems to be a global and relevant criterion that meets the overall objectives of any therapeutic educational action in the care of dementia as well as in most chronic diseases [18],[19]. However, the validity of self-reported QoL assessments for demented patients is a critical issue [20]. Many questions have been raised about the ability of patients with dementia to estimate their QoL [20]. For this reason, self-rating of the QoL is replaced by proxy rating in a large majority of clinical trials involving AD patients, and can be considered a valid outcome [19],[21],[22]. In the THERAD study, we also chose to use the caregiver’s rating of the QoL. We will also raise the reasons for our choice in the Discussion. It has been shown that a multidimensional approach including, but not involving only, therapeutic education could improve the AD patient’s QoL [23].

For all these reasons, it was reasonable to assume that a better understanding of the disease by the family caregiver can have a positive impact on his/her coping strategies and indirectly on the AD patient’s QoL. We therefore designed the THERAD study. The trial addresses community-dwelling patients suffering from mild to moderately severe AD who receive support from a family caregiver. This paper describes the study protocol. In our opinion, when attempting to support the patient/caregiver dyad in AD, therapeutic education is expected to be an especially effective tool, as well as in many chronic diseases [24],[25].

## Methods

### Study design

The THERAD study is a monocentric, randomised, single-blind, controlled trial and has been registered on clinicaltrials.gov since 19 February 2013 [ClinicalTrials.gov: NCT01796314]. The AD patient/caregiver dyads in the intervention group receive a therapeutic educational programme and the dyads in the control group benefit from usual care. The THERAD study will enrol 170 dyads, 85 in the intervention group and 85 in the control group. The entry and follow-up procedures are illustrated in Figure 1. The study protocol was approved by the French Ministry of Health. Informed consent was obtained from all enrolled participants. The Toulouse University Hospital has delivered ethical approval. Blinding of raters is performed in a single-blind experimental design: participants know the full facts (group session), but not the experimenters. The randomisation was done with STATA® Version 11.0. We performed a blocked randomisation. We used a block of four, of fixed size, without stratification. The allocation procedure was conducted by the Department of Epidemiology of the Toulouse University Hospital in Toulouse, France. The randomisation list is printed and kept in this department, protected by a password. At enrolment, a fax is sent by the THERAD study group to this department, together with the participant code and information regarding assignment. The investigators are unaware of the randomisation list. The assignment is concealed for the raters at follow-up visits.

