### Participants

AD patients suffering from mild to moderately severe stages of the disease and their primary caregivers are eligible for inclusion. The diagnosis of AD is based on the clinical criteria of AD according to the *Diagnostic and Statistical Manual of Mental Disorders* (fourth edition) [26]. Each patient undergoes magnetic resonance imaging or a computed tomography scan and biological tests. We are targeting mild to moderately severe stages of the disease defined by the Mini-Mental Score Examination score [27], with scores of 26 to 11/30. We are enrolling community-dwelling patients receiving support from a family caregiver. The caregiver is defined as a nonprofessional person living with the patient or providing support to him/her at least three times a week or for 8 hours a week. Patients of both sexes with no age limit are eligible. Participants are being recruited from the memory clinic and the geriatric units of the Toulouse University Hospital in France. The inclusion period began in January 2013, with an expected duration of 18 months. To date, 107 dyads have been enrolled.

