### Detailed study scheme

The entry and follow-up procedures are illustrated in Figure 1.

All visits are being performed by geriatricians who are hospital practitioners trained in therapeutic education. Written agreement to participate is being obtained from all participants (patients and caregivers).

The baseline visit (M0) concerns both the patient and the caregiver. In both the intervention group (group A) and the control group (group B), the patient receives a consultation led by a geriatrician. This includes a clinical examination and comprehensive geriatric assessment (Mini-Mental Score Examination, weight, one-leg balance, sensorial impairment, co-morbidities, pharmacological and nonpharmacological therapies) [38]. The outcomes concerning the patient are assessed at baseline by: Logsdon QoL-AD reported by the primary caregiver and patient; and the Activities of Daily Living, the Instrumental Activities of Daily Living and the NeuroPsychiatric Inventory reported by the caregiver. The secondary outcomes concerning the caregiver are assessed by the mini-Geriatric Depression Scale, the Zarit Burden Interview and the Nottingham Health Profile, self-reported.

At the end of the baseline visit, each patient/caregiver dyad is randomly allocated to group A or group B (Figure 1). The random number is generated by a computerised generator using block randomisation. The block size is concealed from all researchers. As described in the intervention section and in Figure 1, at the end of the baseline visit the dyads of the intervention group (group A) receive the first step of the intervention: the educational diagnosis (cf. Intervention).

The second 2-month visit (M2) also involves the dyads of both groups A and B, but the first part differs between groups. As described in Intervention, at the beginning of M2 the participants in the intervention group (group A) benefit from the last part of the intervention and its assessment. The participants of both groups then receive a clinical examination, comprehensive geriatric assessment and assessment of endpoints.

Participants in groups A and B receive a follow-up visit at 6 months and at 12 months, including the assessment of the primary and secondary endpoints.

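### The article discloses a fixed block of four while stating that the block size is concealed; a recruiter who saw every earlier allocation could foresee up to one third of assignments

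*Protocol article*

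**What the plan says.** All references are to the Methods of the protocol article.

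- **Scheme.** Study design: "We used a block of four, of fixed size, without stratification". The same section gives one centre ("The THERAD study is a monocentric, randomised, single-blind, controlled trial") and equal arms ("The THERAD study will enrol 170 dyads, 85 in the intervention group and 85 in the control group"), so there is a single 1:1 allocation stream.
- **Concealment.** Detailed study scheme: "The block size is concealed from all researchers". Study design adds that the Department of Epidemiology ran the allocation and keeps the list under a password, that investigators do not know the list, and that raters at follow-up do not know the assignment.
- **When the arm becomes known.** Detailed study scheme: "At the end of the baseline visit, each patient/caregiver dyad is randomly allocated to group A or group B", and then "at the end of the baseline visit the dyads of the intervention group (group A) receive the first step of the intervention". Participants are not blinded: "participants know the full facts (group session), but not the experimenters".
- **Recruitment status.** Participants: "To date, 107 dyads have been enrolled". Recruitment draws on a memory clinic and geriatric units of one hospital.

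**The concern.** The two statements about the block size contradict each other. The study group's own article gives the size as four and fixed, in the same text that reports recruitment as incomplete. Whatever concealment existed before, it cannot be relied on after publication.

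Hiding the list does not by itself hide the next assignment. With a known fixed block in one unstratified stream, the past assignments determine some of the future ones, and past assignments can be observed because group A's first session follows randomisation at the same visit. Someone who can work out the next arm can influence which dyad is booked and when.

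This matters more than usual here because the primary outcome is the caregiver's own rating of the patient's quality of life, made by a caregiver who knows the arm. The Discussion acknowledges that caregiver burden and depression affect that rating. If the kind of caregiver enrolled depended on the expected arm, the primary comparison would be biased. The planned adjustment for disease severity and caregiver burden would not remove imbalance in traits that are not measured.

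**Working it through.** The article gives no figure for predictability, so there is none to reproduce. The inputs are block size 4, ratio 1:1, one stream, 170 dyads planned and 107 enrolled. The counts assume that the list started at a block boundary and that no slots were skipped.

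**1. Allocations fixed by earlier ones.** There are 6 equally likely blocks. In AABB and BBAA the last two allocations are fixed; in the other four only the last is.

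- Expected number per block = (2×2 + 4×1)/6 = 1.333.
- Share = 1.333/4 = 33.3%.
- Chance of certainty by position: 0, 0, 1/3, 1.

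**2. Best guess (always the arm that is behind).** The chance of being right by position is 1/2, 2/3, 2/3, 1. The sum is 2.833, and 2.833/4 = 70.8%, against 50% by chance.

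**3. Counts for this trial.**

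| Stretch | Make-up | Expected number determined |
|---|---|---|
| Dyads 1–107 | 26 blocks, then positions 1–3 of block 27 | 26×4/3 + 1/3 = 35 |
| Dyads 108–170 (63) | position 4 of block 27, 15 blocks, then positions 1–2 | 1 + 15×4/3 + 0 = 21 |
| All 170 | 42 blocks, then positions 1–2 | 42×4/3 = 56 (32.9%) |

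**4. If some allocations go unseen.** Certainty needs both matching earlier allocations to have been seen. If each is missed independently with probability m, the certain share is (1−m)²/3.

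- m = 0.25: 0.5625/3 = 18.8%
- m = 0.50: 0.25/3 = 8.3%

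The article gives no value for m; these two are assumed. A simulation gave 18.7% and 8.4%.

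**5. What varying block sizes would do.** By simulation over 170 dyads, a full observer who knows only the set of possible sizes can predict about 5% with certainty for a random mix of 4 and 6, and about 2% for 4, 6 and 8. Best guessing improves much less. Fixed blocks of 6 and 8 give 68.3% and 66.6% correct, so an equal mix of 4, 6 and 8 gives (2.833 + 4.100 + 5.329)/18 = 68.1% for someone who still sees every allocation.

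**The case against.** Several points on the other side are sound.

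- **One third is a ceiling.** It needs a recruiter who knows the block size, knows where blocks begin and has seen every earlier allocation. The article describes no shared allocation log. Several units recruit, more than one geriatrician runs visits, and it is not said who delivers the educational diagnosis at the baseline visit. This stands, and is why a range is given.
- **Real safeguards exist.** A separate department holds the list, and randomisation follows the baseline assessments, so baseline scores are recorded before the actual assignment. This also stands. The remaining route is the choice of whom to enrol and when.
- **The 63 dyads are counted at the time of writing, not of publication.** The article already mentions attrition at the 12-month visit, so it was written in January 2014 or later. Inclusion was expected to run 18 months from January 2013. Fewer than 63 may have been left when the block size became public, so 21 is an upper figure.
- **A fixed small block with central allocation is a recognised choice.** That is true, but it does not resolve the contradiction over concealment.

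A reader might infer that enrolling clinicians knew the block size from the start, or that enrolment was steered towards motivated caregivers. The article supports neither. Those who wrote that they used a block of four may include the department that ran the randomisation, and nothing describes steering. A fixed block of four could, however, be worked out by anyone who watched the sequence.

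**Conclusion.** The concern holds in conditional form. The firm defect is the contradiction: the block size is said to be concealed from all researchers and is disclosed in the same article. The consequence is a risk of selection bias. Up to 33% of allocations could be known with certainty and 71% guessed correctly, with up to about 21 of the 63 dyads outstanding at the time of writing affected. These figures assume knowledge of the block size, full observation of earlier allocations and a list that started at a block boundary. With incomplete observation the certain share is lower, at about 19% or 8% under the assumed miss rates. It would be wrong to say that a third of allocations were in fact predicted, or that the trial's result is biased. The matter deserves correction because the remedy is cheap and the primary outcome is rated by an unblinded caregiver.

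**What to change.** 1. **For dyads not yet randomised**, have the Department of Epidemiology issue a new list with randomly varying block sizes (for example 4, 6 and 8), with neither the sizes nor the set disclosed to anyone who enrols. This is one regenerated list. The arms may end a few dyads apart, but exactly 85 and 85 is not guaranteed now either: 170 = 42×4 + 2, and a last block cut after two is balanced with probability 2/3. The change removes nearly all certain predictions but not educated guessing by someone who tracks every allocation. If recruitment has closed, this step no longer applies.
2. **Correct or delete the statement that the block size is concealed**, or limit it to the new list. This costs nothing.
3. **If a check on dyads already enrolled is wanted**, compare baseline characteristics between arms according to whether the allocation was predictable, for example by predicted arm. Do not pool all determined allocations against all undetermined ones: favourable dyads steered to one arm and unfavourable dyads to the other would cancel. State the low precision. About 35 determined allocations are expected among the first 107, or 17.5 per arm. With the planned SD of 5.5, the 95% half-width for a baseline difference is 1.96 × 5.5 × √(2/17.5) = 3.6 points, wider than the 2.6 points (5% of 52) that the trial is sized to detect. A null result would therefore reassure little.

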**Figure 1 F1:**
[figure not shown]
**Entry and follow-up procedures of the THERAD study.** MMSE, Mini-Mental State Examination; THERAD, Therapeutic Education in Alzheimer’s Disease.

### Participants

AD patients suffering from mild to moderately severe stages of the disease and their primary caregivers are eligible for inclusion. The diagnosis of AD is based on the clinical criteria of AD according to the *Diagnostic and Statistical Manual of Mental Disorders* (fourth edition) [26]. Each patient undergoes magnetic resonance imaging or a computed tomography scan and biological tests. We are targeting mild to moderately severe stages of the disease defined by the Mini-Mental Score Examination score [27], with scores of 26 to 11/30. We are enrolling community-dwelling patients receiving support from a family caregiver. The caregiver is defined as a nonprofessional person living with the patient or providing support to him/her at least three times a week or for 8 hours a week. Patients of both sexes with no age limit are eligible. Participants are being recruited from the memory clinic and the geriatric units of the Toulouse University Hospital in France. The inclusion period began in January 2013, with an expected duration of 18 months. To date, 107 dyads have been enrolled.

### Sample size

We hypothesise a similar QoL score in the two groups at baseline, 25 ± 5.5 points (Logsdon Quality of Life in Alzheimer’s disease (QoL-AD) scale including 52 points [28]). To detect an increase of 5% in the total score and a relative variation of more than 10% of the baseline score between trial arms, with an alpha risk of 5% and a beta risk of 20%, and anticipating 20% attrition, 85 dyads are required per group. The total sample size required for the study is 170 dyads (85 per arm).

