### Analysis

Data are collected in the Access database and SAS software (developped by the SAS institute based in Cary, North Carolina, USA) will be used to perform the statistical analysis. Intention-to-treat analysis using a linear mixed model will be performed, adjusting for patient (disease severity) and caregiver (burden) characteristics and occurrence of life events that may interfere with the patient’s QoL. Attrition of dyads has been taken into account. At the moment, at the 12-month visit, there is less than 5% attrition. Moreover, the total sample size required for the study was calculated anticipating a risk of 20% attrition to take into account this phenomenon, which is particularly important in our population [45].

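### On the article's own inputs, 85 dyads per arm give about 78–79% power at 20% attrition, not 80%; the stated combination needs about 89 per arm (minor)

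*Protocol article*

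**What the plan says.** The Sample size section gives all the inputs except the sidedness of the test. The outcome assumption is "We hypothesise a similar QoL score in the two groups at baseline, 25 ± 5.5 points", on a "scale including 52 points". The target is put in two ways: a rise equal to 5% of the total score, and a between-arm difference exceeding one tenth of the baseline value. The conclusion is "with an alpha risk of 5% and a beta risk of 20%, and anticipating 20% attrition, 85 dyads are required per group", hence 170 in total.

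The Analysis section returns to the allowance, saying that "the total sample size required for the study was calculated anticipating a risk of 20% attrition", and reports that so far, "at the 12-month visit, there is less than 5% attrition".

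The article does not print the formula, the evaluable number before inflation, or the way the 20% was applied.

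**The concern.** An allowance for 20% loss means that 80% of those randomised must be enough for the analysis, so the evaluable number is divided by 0.8. Multiplying it by 1.2 gives a smaller number, and the figure of 85 fits the multiplication rather than the division. If so, the four printed elements (2.6 points, 80% power, 20% attrition, 85 per arm) cannot all hold together. At stake is whether the published power statement is true under the attrition that it names.

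**Working it through.** **Inputs** (Sample size section unless noted)

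- SD 5.5, taken as the SD of the quantity compared between arms.
- Difference: 5% × 52 = 2.6 points. As a share of baseline this is 2.6/25 = 10.4%, so the second wording of the target is also met.
- Alpha 5%, two-sided by assumption because the article does not say; power 80%.
- Allocation 1:1 (Study design section); attrition 20%.

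**Evaluable number per arm**

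n = 2(z₀.₉₇₅ + z₀.₈₀)² × SD² / δ² = 2 × (1.960 + 0.8416)² × 5.5² / 2.6² = 70.25, i.e. 71. The t-test version gives 71.22, i.e. 72.

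**Reproducing the printed 85**

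| Start | × 1.2 | ÷ 0.8 |
|---|---|---|
| 70.25 (unrounded) | 84.3, up to 85 | 87.8, up to 88 |
| 71 | 85.2 | 88.75, up to 89 |
| 72 (t-test) | 86.4 | 90 |

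Multiplication by 1.2 recovers 85 or comes within about one dyad of it. Division by 0.8 gives 88 to 90.

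**Other readings of the inputs, divided by 0.8**

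- 2.5 points, two-sided: 95 to 97 per arm.
- 2.75 points, two-sided: 79 to 80 per arm.
- 2.6 points, one-sided: 70 to 72 per arm.
- SD 5.45, the lowest value that rounds to 5.5, with 2.6 points: 68.97/0.8 = 86.2, i.e. 87 per arm.

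None of these gives 85.

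**What 85 per arm delivers at 2.6 points and SD 5.5**

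| Loss | Evaluable per arm | Power, normal | Power, t-test |
|---|---|---|---|
| 20% | 85 × 0.8 = 68 | 78.7% | 78.1% |
| 5% | 85 × 0.95 = 80.75; figures for 80 | 84.9% | 84.4% |
| 0% | 85 | 86.9% | 86.5% |

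**Largest attrition at which 80% power is kept**

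- t-test, 72 needed: 1 − 72/85 = 15.3%.
- Normal formula, 71 needed: 1 − 71/85 = 16.5%.

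**Number that would match the stated claim**

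89 per arm, 178 in total: 4 more per arm and 8 more overall than stated (90 per arm by the t-test).

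**The case against.** Several counter-arguments have force.

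- **The cause is not shown.** The article prints no inflation step. Division by 0.8 gives exactly 85 if the unrounded difference was about 2.64 points, because 68 evaluable per arm carry 80% power for 2.64 points by the normal formula. A reader might infer that the authors certainly multiplied by 1.2. The text supports only that this is the best fit. The mismatch itself does not depend on the cause: with the printed 2.6 points and SD 5.5, 85 is too few for 80% power at 20% loss.
- **The loss of power is small.** It is 1.3 to 1.9 points, less than the uncertainty in any assumed SD. This stands and sets the severity.
- **The condition may not arise.** The primary endpoint is at 2 months, and attrition below 5% is reported at 12 months. This also stands as regards the trial's prospects, although the article does not say how many of the 107 enrolled dyads had reached 12 months. It does not make the planning sentence correct at 20%.
- **The planned model may be more efficient.** If the linear mixed model used the baseline score as an ANCOVA does, a correlation between baseline and 2 months of about 0.18 (normal) to 0.21 (t-test) would restore 80% at 68 per arm. The article gives no such correlation and does not credit it in the calculation, so this is a possible gain rather than a justification of the figure.

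Two stronger readings should be left aside. A reader might take 2.5 points as the target and quote 74.9% power (t-test) at 68 per arm. However, the article asks for more than 10% of baseline, which excludes exactly 2.5 points, and 2.5 points with × 1.2 would give 91 to 92 rather than 85. A reader might also call the Analysis section's statement about attrition untrue. It is not: an allowance was made, and that section does not restate the power.

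**Conclusion.** The concern holds as a minor error in a stated figure. For 2.6 points, SD 5.5, two-sided 5% and 80% power, 20% attrition calls for about 89 dyads per arm (88 to 90 according to rounding and formula), against 85 stated. At 85 per arm and 20% loss, power is about 78–79%. The allowance built into 85 covers a loss of about 15% (t-test) or 16.5% (normal formula).

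A reader might infer that the trial is underpowered. The documents do not support that: the shortfall is under 2 points even at the full 20%, and at 5% loss power is about 84–85%, above the target.

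The conclusion rests on a two-sided test and on SD 5.5 applying to the compared outcome. A one-sided test or a 2.75-point target would remove the shortfall, but neither is stated and neither leads to 85.

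**What to change.** Keep 170 dyads. In the Sample size section, state the sidedness, the evaluable number per arm (71 by the normal formula, 72 by the t-test) and how the 20% was applied. Replace the power claim with wording such as: 85 dyads per arm give about 78% power (two-sided t-test, difference 2.6 points, SD 5.5) if 20% are lost, and keep 80% power for attrition up to about 15%. If the normal formula is used instead, the matching figures are about 79% and 16.5%; name the method so that the two are not mixed.

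The cost is one or two corrected sentences. No extra dyads are needed, and the design, endpoint and analysis do not change. The stated power at 20% attrition becomes slightly less favourable.
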